## Abstract

**Background::**

It has not been determined that demand valve oxygen therapy is effective for nocturnal hypoxia. A portable oxygen concentrator with an auto-demand oxygen delivery system (auto-DODS; standard, high, and extra high) has recently been developed to improve oxygenation and comfort. This oxygen concentrator can supply a pulsed flow when it detects apnoea. The aim of this study is to demonstrate that this newly developed portable oxygen concentrator with an auto-demand function is non-inferior to a continuous-flow oxygen concentrator for nocturnal hypoxemia.

**Methods::**

Twenty patients with chronic obstructive pulmonary disease or interstitial pneumonia will be randomized to receive a portable oxygen concentrator with an auto-DODS or a continuous-flow oxygen concentrator during sleep. The primary endpoint is mean oxygen saturation (SpO_2_) during the total sleep time. The secondary endpoints are the ratios of time that the oxygen concentrator spends in each sensitivity mode (standard, high, and extra-high) and at a constant pulse rate to the total sleep time, the total time and ratio of time for which SpO_2_ is less than 90% during the total sleep time, the lowest value of SpO_2_ during the total sleep time, the mean and highest pulse rate during the total sleep time, the apnoea index during the total sleep time, the total sleep duration itself, and comfort and reliability as measured by numerical rating scale and questionnaires.

**Discussion::**

If the auto-DODS demonstrates non-inferiority to continuous flow in oxygenation during sleep, the auto-DODS can be used even at night, and the patient will need only 1 device.

**Trial Registration::**

The study was registered on Aug 23, 2019 (jRCTs052190042).

## Introduction

1

Long-term oxygen therapy (LTOT) is reported to improve hypoxemia and survival and has become an essential treatment for patients with respiratory failure caused by chronic obstructive pulmonary disease (COPD), interstitial pneumonia, and other conditions.^[1]^ There are 3 types of LTOT: gaseous oxygen, portable liquid oxygen systems, and stationary oxygen concentrators. Portable liquid oxygen systems are generally used outside the home, and stationary oxygen concentrators are used at home. A respiration synchronizer (demand oxygen delivery system [DODS]) is a device that supplies oxygen from the oxygen cylinder only when the user is inhaling, thereby saving oxygen and extending the usable life of the oxygen cylinder by 2 to 3 times. Tiep et al compared DODS oxygen and continuous-flow oxygen in 10 chronic respiratory disease patients. At rest, the DODS was equivalent to continuous flow: oxygen saturation (SpO_2_) was 93.7% ± 2.1% with an DODS and 93.8% ± 1.9% with continuous flow. During exercise at corresponding settings, the SpO_2_ with low flow through a DODS was 90.5% ± 3.8%, the SpO_2_ with high flow through a DODS was 92.5% ± 2.8% and the SpO_2_ with continuous flow was 93.1% ± 3.1%.^[2]^ Garrod et al conducted a randomized controlled trial of a continuous-flow system and a DODS in 14 COPD patients and revealed that there was no significant difference in the mean arterial oxygen saturation between patients who used the DODS and those who received continuous-flow oxygen (*P* = .33). Furthermore, there was no significant difference between the distance walked using oxygen delivered at 2 L/min by continuous flow and via the DODS (*P* = .72; confidence interval [CI] 0.34–1.08).^[3]^ The conventional demand device is a portable oxygen concentrator and has a conventional demand mode. This conventional demand device detects the negative pressure gradient of inspiration and supplies oxygen only during inspiration, sounding an alarm only if there is no breathing for 3 minutes. On the other hand, the newly developed auto-demand device is an oxygen concentrator that has an auto-demand mode. This auto-DODS can automatically switch among 3 sensitivity modes – extra-high, high and standard – according to the negative pressure and the supply of oxygen specifically at the time of inhalation. Moreover, if there is no breathing for a fixed time, the system can deliver oxygen at a constant pulse rate in addition to sounding an alarm.

## Material and methods

2

### Aim

2.1

The aim of this study is to examine whether clinically important indices during sleep are comparable between oxygen delivery by an auto-DODS and by continuous flow.

### Design and setting

2.2

All study endpoints are listed as bullet points in Table 1. This is a randomized open-label crossover noninferiority trial of an auto-DODS versus continuous flow during sleep by patients who are prescribed LTOT for COPD or interstitial pneumonia. In the present study, patients will use an auto-DODS or continuous flow at night in random order. Patients will be hospitalized for 2 nights and use different devices on the first and second nights. The auto-DODS will not be used during the day. Therefore, no carryover effect will occur. The data will be collected in the Kobe University Hospital in Kobe, Japan. The study design will be outlined in Figure 1.

**Table 1 T1:**
[figure not shown]
Primary and secondary endpoints addressed by this study protocol.

**Figure 1 F1:**
[figure not shown]
Flow chart of the study. COPD = chronic obstructive pulmonary disease, DODS = demand oxygen delivery system, IP = interstitial pneumonia, LTOT = long-term oxygen therapy.

### Participants

2.3

The inclusion and exclusion criteria for the trial are listed in Table 2. Participants who are outpatients of the Kobe University Hospital will be recruited.

**Table 2 T2:**
[figure not shown]
Inclusion and exclusion criteria.

### Materials

2.4

Patients who are enrolled in this clinical trial and use the test devices will be analyzed. According to the results of the previous study using continuous flow and an auto-DODS (the sensitivity was fixed at extra-high) at night for LTOT patients, the difference in the mean value of SpO_2_ between the continuous-flow group and the auto-DODS group was 1.8%, with a higher mean SpO_2_ in the continuous-flow group than in the auto-DODS group. The non-inferiority margin was set to 2.8%, which corresponded to 70% of the minimal clinically important difference (± 4%) in SpO_2_.^[4]^ Based on the SpO_2_ difference of 1.8% between continuous flow and the auto-DODS, the 1.4% standard deviation of the difference, and the noninferiority margin of 2.8%, we calculated, for an alpha level of 2.5% and a statistical power of 80%, that a sample size of 8 per group was needed. The formula used for the calculation is as follows: 

The sample size in this clinical study was set to 10 patients per group, in anticipation of a dropout rate of approximately 20%.

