### Statistical analysis

2.7

The primary aim of this trial is to test the noninferiority of the auto-DODS to a continuous-flow system in maintaining night-time SpO_2_. Based on the assumption that there is no carryover effect for treatment, we will analyze all eligible participants whose SpO_2_ data during the use of the 2 devices can be obtained. To test the noninferiority of the DODS, we will set the noninferior margin of the mean night-time value of SpO_2_ to Δ (= 2.8%). The null hypothesis H0 of the hypothesis test for noninferiority verification is *μ*1 ≦ *μ*_0_ − Δ, and the alternative hypothesis H1 is *μ*_1_ > *μ*_0_ − Δ, where *μ*_0_ is the population mean of SpO_2_ with a continuous-flow system, while *μ*_1_ is the population mean of SpO_2_ with an auto-DODS. If the lower limit of the estimated 95% CI for the difference of population means between the auto-DODS and continuous flow is above –Δ, we will regard the auto-DODS as noninferior. We will conduct a statistical test for noninferiority to calculate the *P*-value, with a 1-sided significance threshold of 2.5%.

We will also analyze secondary endpoints under the assumption that there is no carryover effect. The difference in the population means of SpO_2_ between the auto-DODS and continuous flow will be estimated, along with its 95% CI.

We will also conduct an analysis of variance that includes group, period, and device for the primary and secondary endpoints. Furthermore, as the subanalysis, we will estimate the difference in the population mean of each outcome, along with its 95% CI, between the auto-DODS and continuous flow using only the outcomes from the first period and will calculate the *P*-value based on Student *t* test or the Wilcoxon test.

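### The 80% power claimed for 8 patients per group appears to rest on a normal approximation; with a t-based interval the same 16 evaluable patients give about 76%

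*Protocol article*

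**What the plan says.** The inputs to the sample size are in the Materials section (2.4) of the protocol article. The assumed difference in mean SpO2 "between the continuous-flow group and the auto-DODS group was 1.8%, with a higher mean SpO_2_ in the continuous-flow group". The other two inputs are "the 1.4% standard deviation of the difference, and the noninferiority margin of 2.8" percentage points. The stated result is "for an alpha level of 2.5% and a statistical power of 80%, that a sample size of 8 per group was needed". The enrolment target follows: "The sample size in this clinical study was set to 10 patients per group, in anticipation of a dropout rate of approximately 20" per cent. The abstract agrees on the total: "Twenty patients with chronic obstructive pulmonary disease or interstitial pneumonia will be randomized".

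Design and setting (2.2) fixes the design: "This is a randomized open-label crossover noninferiority trial of an auto-DODS versus continuous flow during sleep". Each patient uses both devices, one on each of two nights, so "group" has to mean the sequence group, and 8 per group means 16 evaluable patients.

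Statistical analysis (2.7) declares non-inferiority if the lower limit of the 95% confidence interval for the mean difference (auto-DODS minus continuous flow) lies above minus 2.8, and adds a test "with a 1-sided significance threshold of 2.5" per cent. It analyses patients with SpO2 data on both devices. It does not name the primary test. An analysis of variance with group, period and device is planned in addition, and Student's t test or the Wilcoxon test is named only for the first-period subanalysis.

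**The concern.** At about 16 patients, the choice between normal and t quantiles can change the integer answer of a sample size calculation. With 14 to 15 error degrees of freedom the two-sided 95% critical value is 2.14 to 2.13, not 1.96. If the sample size was found with 1.96 and the interval is then built with the larger value, the trial has less power than stated.

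The dropout allowance makes this matter. It is set so that the expected losses bring the trial down to exactly 16 evaluable patients, so the stated power has no reserve in the scenario the plan itself anticipates. A reader of an inconclusive result would take the chance of failure, on the planning assumptions, to be 20%, when it would be about 24%.

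**Working it through.** **Inputs**, all from the protocol article:
- assumed deficit of auto-DODS: 1.8 points (Materials)
- SD of the difference: 1.4 points (Materials)
- margin: 2.8 points (Materials), so the distance to the margin is 2.8 − 1.8 = 1.0
- one-sided alpha 2.5% (Statistical analysis), power 80% (Materials)
- 20 enrolled and about 20% dropout, so 20 × 0.8 = 16 evaluable

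**Step 1: reproduce the plan's figure.** For a within-patient comparison with normal quantiles:

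N = [SD × (z0.975 + z0.80) / distance]² = [1.4 × (1.960 + 0.842) / 1.0]² = 15.38

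That is 7.69 per sequence, rounded up to 8, or 16 in total. Then 8 / (1 − 0.2) = 10 per group. Both printed figures are matched. Normal-approximation power at 16 is Φ(1.0 × √16 / 1.4 − 1.960) = 81.5%.

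Other readings do not fit. Two parallel arms with the same inputs would need 31 per arm. Eight patients in total would give 52% power with normal quantiles or 41% with t. A t-based crossover calculation would have returned 9 per sequence, not 8.

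**Step 2: power with t quantiles.** The noncentrality parameter is 1.0 × √N / 1.4, which is 2.857 at N = 16. Power is the probability that a noncentral t variable exceeds the central 97.5% quantile. A paired analysis has N − 1 degrees of freedom; a two-sequence crossover analysis with a period effect has N − 2.

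| Evaluable | Lost of 20 | Paired, N − 1 df | Crossover, N − 2 df |
|---|---|---|---|
| 16 | 4 | 76.1% | 75.7% |
| 17 | 3 | 79.0% | 78.6% |
| 18 | 2 | 81.5% | 81.2% |
| 19 | 1 | 83.7% | 83.5% |
| 20 | 0 | 85.8% | 85.5% |

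A simulation of 400,000 trials with 16 patients gave 76.2% (paired) and 75.8% (crossover).

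**Step 3: where 80% is reached.** The smallest size with at least 80% is 18 evaluable, 9 per sequence. With 20 enrolled, that tolerates two losses (2/20 = 10%), not the four (4/20 = 20%) that are planned for.

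**Step 4: scale against the other inputs.** With 16 evaluable patients and 14 degrees of freedom, changing one input at a time in both directions:
- difference 1.6 instead of 1.8: 89%; difference 2.0: 57%
- SD 1.2 instead of 1.4: 87%; SD 1.6: 64%

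**The case against.** The strongest reply is that nothing has been miscalculated. Inputs, rounding and dropout inflation agree with one another, and a formula with normal quantiles is a common planning tool. That stands: this is a small-sample approximation, not a slip of arithmetic.

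Two links in the argument are inferences. The formula is missing from the text at hand, so the use of normal quantiles is deduced from the exact match; if the published formula shows them, the approximation is already disclosed. The primary test is not named either, and its exact form may be left to an analysis plan that is not shown. Both caveats stand. A normal interval would not rescue the 80%, however. With the SD estimated from 16 patients, a cut-off of 1.96 has a one-sided error of about 3.4% (the upper tail of t with 15 degrees of freedom), above the stated 2.5%.

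It is also fair to say that 76% applies only if the dropout allowance is used up. The trial randomises 20 patients for two inpatient nights, and with two losses or fewer the power exceeds 80%.

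A reader might infer more: that the trial is underpowered as designed, or that power is fragile because the 1.8 came from a device fixed at extra-high sensitivity. The documents support neither. Power is above 80% at 18 to 20 evaluable patients. The source of the 1.8 is disclosed, and the Discussion predicts that the three sensitivity levels and the apnoea response will keep the auto-DODS non-inferior, so nothing indicates that the true deficit is larger than 1.8 rather than smaller. Sensitivity to the assumed difference is general to trials planned near a margin and is a separate matter.

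**Conclusion.** The point holds in a limited form. On the plan's own inputs, and with a t-based interval, 8 evaluable patients per sequence give 75.7% to 76.1% power, about 4 points below the stated 80%. Reaching 80% takes two more evaluable patients, 18 in place of 16. The shortfall occurs only if at least three of the 20 are lost, and the planned dropout of about 20% would do that.

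This rests on three assumptions: that "group" means sequence group, which is the only reading tried that reproduces the printed figure; that normal quantiles were used, which is inferred; and that the primary interval is t-based, which is the natural reading but is not stated. The type I error, the estimate and the decision rule are not affected. The weight is modest: a printed power figure should be corrected, and the design need not change.

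**What to change.** Restate the power in the Materials section, for example: 16 evaluable patients give about 76% power (t-based); 80% power requires 18 evaluable patients, that is, dropout of at most 10%; all 20 give about 86%. Say in the same place which quantiles the original formula used.

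Sensitivity figures are optional. If they are given, show them in both directions, as in the last step of the working, and not only for less favourable values.

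The cost is a few lines of text and a slightly less favourable printed figure. Enrolment, margin, alpha and the analysis stay as they are.

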### Processes and interventions

2.5

A steering committee including principal investigator and co-investigator are responsible for design, methodology and protocol amendments of the study. The principal investigator and co-investigators will conduct observations, inspections, and evaluations according to the following schedule.

After obtaining consent, the investigators will start the screening test. The patient characteristics to be assessed are summarized in Table 3. The principal investigator and co-investigators will identify patients who meet the inclusion criteria and do not meet the exclusion criteria and will include them as study subjects. On day 1, participants will be assigned to either an auto-DODS or continuous flow, which will be adjusted so that the level of SpO_2_ is the same in both conditions, and the participants will undergo polysomnography and complete a questionnaire (Table 4). On day 2, each participant will be assigned to the opposite device and will undergo polysomnography and a questionnaire once again. Participants will be checked for adverse events that are experienced during the treatment period until day 30.

**Table 3 T3:**
[figure not shown]
Patient characteristics.

**Table 4 T4:**
[figure not shown]
Questionnaire.

The principal investigator and co-investigators will create a “facility registration/user registration request form” and will send it to the data center. The principal investigator will receive and will retain the approval of the accredited clinical research review board and the administrator. After confirming that this trial has been published in the Japan Registry of Clinical Trials, the data center will perform facility registration and user registration based on the registration request forms and notifies the investigator of registration completion by E-mail.

The investigators will access the electronic data capture (EDC) using a user ID and password prepared in advance and input the case report data for each subject into the EDC. After confirming that the created case report form is correct, the principal investigator will electronically sign the EDC. The signed case report form will be printed and stored. If the data center inquires about input data, the principal investigator will confirm the content of the EDC and respond promptly.

Monitoring will be conducted regularly to confirm that this clinical trial is being conducted safely, in accordance with the study protocol version 2.0, and that data are being correctly collected. The principal investigator will appoint a monitoring supervisor and a monitor. The monitoring supervisor and the monitor must learn the regulatory requirements for clinical research and must fully understand the contents of the research protocol and monitoring procedures. During the study period, the monitor will directly check the consent sheets, medical records, and case reports. The monitor will perform these monitoring duties before, during, and after the trial.

To guarantee the quality of this clinical trial, we will evaluate whether this trial is being conducted in compliance with the study protocol and procedures, independent of the normal monitoring and quality control operations conducted by audit. The principal investigator will appoint an auditor and have that person carry out the audit in accordance with the audit procedure manual. The auditor will report the results of the audit to the principal investigator.

During monitoring, audits, and regulatory reviews related to clinical trials, the principal investigator, and medical institution will provide for direct review all records related to the clinical trial.

### Comparison

2.6

Analysis will be performed after the use of the devices has ended in all cases and the data are fixed. In all efficacy evaluations, analysis of the full analysis set, comprising all subjects who use the test device, will be used as the main analysis, and analysis of the per-protocol set, including only subjects who followed the full protocol with no violations, will be performed as a reference. For the safety analysis, we will analyze a safety analysis set that includes all subjects who use a test device.

### Statistical analysis

2.7

The primary aim of this trial is to test the noninferiority of the auto-DODS to a continuous-flow system in maintaining night-time SpO_2_. Based on the assumption that there is no carryover effect for treatment, we will analyze all eligible participants whose SpO_2_ data during the use of the 2 devices can be obtained. To test the noninferiority of the DODS, we will set the noninferior margin of the mean night-time value of SpO_2_ to Δ (= 2.8%). The null hypothesis H0 of the hypothesis test for noninferiority verification is *μ*1 ≦ *μ*_0_ − Δ, and the alternative hypothesis H1 is *μ*_1_ > *μ*_0_ − Δ, where *μ*_0_ is the population mean of SpO_2_ with a continuous-flow system, while *μ*_1_ is the population mean of SpO_2_ with an auto-DODS. If the lower limit of the estimated 95% CI for the difference of population means between the auto-DODS and continuous flow is above –Δ, we will regard the auto-DODS as noninferior. We will conduct a statistical test for noninferiority to calculate the *P*-value, with a 1-sided significance threshold of 2.5%.

We will also analyze secondary endpoints under the assumption that there is no carryover effect. The difference in the population means of SpO_2_ between the auto-DODS and continuous flow will be estimated, along with its 95% CI.

We will also conduct an analysis of variance that includes group, period, and device for the primary and secondary endpoints. Furthermore, as the subanalysis, we will estimate the difference in the population mean of each outcome, along with its 95% CI, between the auto-DODS and continuous flow using only the outcomes from the first period and will calculate the *P*-value based on Student *t* test or the Wilcoxon test.

## Discussion

3

There has been only 1 report evaluating the nocturnal efficiency of a DODS.^[5]^ In that report, the DODS reduced oxygen usage by 60%. Although the DODS and continuous flow were not significant different in oxygenation or sleep quality, the continuous-flow system tended to be somewhat superior in oxygenation. Since the auto-DODS, in contrast to a conventional DODS, has 3 levels of sensitivity and a function that generates a pulsed flow in response to apnoea, we predict that the auto-DODS will not be inferior to continuous flow in oxygenation or sleep quality.

A limitation of this study is that we cannot assess the long-term prognostic impact of the auto-DODS. However, we believe that if the safety and efficacy of the auto-DODS are confirmed in 2 different disease states, COPD and interstitial pneumonia, it will be an advantage for many patients.
